#### Secondary Outcome Measures: Health-Related Quality of Life (Chronic Respiratory Questionnaire – CRQ)

This questionnaire is already validated and translated into Portuguese [21]. It consists of 20 questions divided into 4 domains: fatigue (4 questions), dyspnea (5 questions), emotional function (7 questions), and self-control (4 questions). The responses will be assessed via a Likert scale, with 7 alternatives ranging from “never” to “always,” whereas the dyspnea domain includes an individualized assessment in which the patient chooses, from a list of 26 daily activities, the 5 activities that cause the most dyspnea and then rates each one again via a Likert scale with 7 alternatives ranging from “unbearable shortness of breath” to “no shortness of breath.” The results will be expressed as the mean score of each domain and the total score, with higher scores indicating better HRQoL.

### Anxiety and Depression Symptoms

The HADS will be used to assess anxiety and depression symptoms. The questionnaire was developed to identify symptoms of anxiety and depressive mood and has been translated, validated, and published in Portuguese by Botega et al [22]. It consists of 14 multiple-choice questions divided into 2 subscales, anxiety (HADS-A) and depression (HADS-D) symptoms, with 7 questions each. The domains are categorized by the severity of the stress present: none, 0‐7; probable, 8‐10; and present, ≥11 [23,24].

### Health Status

Health status will be assessed by the CAT, a specific questionnaire for COPD that assesses the impact of the disease’s symptoms [1]. It consists of 8 items related to health conditions and has been applied and validated in several languages, including Portuguese [25].

### Sample Characterization

#### Initial Assessment

Individuals will undergo an initial interview to provide information on several aspects: identification and contact data, medical history (eg, depression, osteoarthritis or arthrosis, osteoporosis, diabetes mellitus, and arterial hypertension), and current medications.

#### Lung Function

Pulmonary function parameters will be obtained from the individual’s medical records within the previous 6 months. The interpretation will be performed according to the standards of the American Thoracic Society and European Respiratory Society [26] and normal values relative to the Brazilian population [27].

#### Physical Activity in Daily Life

The PADL will be quantified using a triaxial accelerometer (GT9X; ActiGraph) for sample characterization. The equipment will be placed on the individual’s waist, and the individual will be advised to wear it for 7 days and only remove it to sleep and shower. They will be instructed to maintain their lifestyle habits. Seven full days of monitoring will be considered to evaluate the PADL: 5 weekdays and 2 weekend days. Zero counting time (considered the period in which the participant did not use the accelerometer) or days with less than 8 hours of device use will be excluded [28]. The results will be expressed as the time of sedentary behavior, steps per day, and time spent in moderate to vigorous physical activity.

#### Statistical Analysis

Data normality will be assessed using the Shapiro-Wilk test, and homoscedasticity will be assessed using the Levene test. Continuous variables will be presented as mean (95% CI) or as medians and IQRs, according to their distribution. Intergroup comparisons will be performed using 2-way ANOVA for repeated measures with Bonferroni post hoc correction or the Kruskal-Wallis test with Dunn test when assumptions are violated. The proportion of individuals not reaching the minimal clinically important difference will be compared using the chi-square test. Within-group effect sizes (Cohen *d*) will be classified as small (0.2), moderate (0.5), or large (0.8). The Spearman correlation coefficient will be used to analyze the associations between changes in ESWT time and changes in CAT, HADS-A, HADS-D, and CRQ scores. Analyses will be conducted according to the intention-to-treat principle, using GraphPad Prism version 5.0, with significance set at *P*<.05.

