#### Sample Calculation

The sample size calculation was based on the primary outcome, based on a previous study showing a mean difference of 65 (SD 65) seconds between groups in the ESWT [29]. Thus, considering an alpha of .05 and a beta of .80, the estimated sample size will be 17 individuals per group. To account for potential losses and to allow for data imputation under the intention-to-treat principle, the sample size was increased by 20% in each group. Therefore, the final estimated sample size was 21 participants per group.

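### A baseline-adjusted ANCOVA would estimate the between-arm tape effect more efficiently than the planned repeated-measures ANOVA, and the within-group Cohen d cannot show that effect

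*Protocol article*

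**What the plan says.** The Statistical Analysis section of the protocol article sets the between-arm analysis: "Intergroup comparisons will be performed using 2-way ANOVA for repeated measures with Bonferroni post hoc correction". A Kruskal-Wallis test with Dunn's test replaces it when assumptions fail. No baseline covariate is planned. The effect sizes are described as "Within-group effect sizes" (Cohen d), with the usual small, moderate and large labels. The section also plans means with 95% CIs and a chi-square comparison of the proportions that miss the minimal clinically important difference.

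The Sample Calculation section sizes the trial on a "mean difference of 65 (SD 65) seconds between groups in the ESWT", with the result that "the estimated sample size will be 17 individuals per group", raised to 21. According to the Experimental Design section, the ESWT is measured in everyone at baseline and again after the programme.

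**The concern.** The Objective in the Abstract is the additional effect of ET in patients who all receive pulmonary rehabilitation. That is a between-arm quantity.

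- **Effect size.** A within-group Cohen d measures everything that changes between the two assessments: rehabilitation, time and tape together. It can be large in both arms even if the tape does nothing. No between-arm effect size is named beside it.
- **Efficiency.** With two time points, the interaction subtracts the whole baseline value, as if the baseline-to-post slope were 1. ANCOVA estimates that slope and so leaves less residual variance whenever r is below 1. In a trial of 21 per arm, with 10 patients recruited by November 2025 (Results section), lost precision is expensive.

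**Working it through.** **Inputs.** Difference 65 s, SD 65 s, 17 per arm before losses and 21 after (Sample Calculation). Alpha is .05; two-sided is assumed, since the side is not stated. The article writes "considering an alpha of .05 and a beta of .80"; the .80 is read as power, because only that reproduces the sample size. The correlation r is not given and is assumed over 0.3 to 0.9. The article does not say whether 65 s is the SD of change or of the post-programme score, so both readings are shown. Equal SDs at the two time points are assumed.

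**The plan's own figure.** For a two-sample t-test the standard error at 17 per arm is 65 × √(2/17) = 22.3 s, so the noncentrality is 65/22.3 = 2.92 on 32 degrees of freedom. Power is 0.807; 16 per arm gives 0.781. The stated 17 is reproduced. Then 17 × 1.2 = 20.4, rounded up to 21.

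**Variances.** Let s be the SD at each time point.
- Interaction (t-test on change): 2s²(1−r)
- ANCOVA: s²(1−r²), with one residual degree of freedom fewer (31)
- Ratio ANCOVA/interaction: (1−r²)/[2(1−r)] = (1+r)/2

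The variance saving is therefore (1−r)/2: 35% at r = 0.3, 25% at 0.5, 15% at 0.7, 10% at 0.8 and 5% at 0.9.

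**Reading 1: 65 s is the SD of change.** The interaction SD is 65 s throughout; the ANCOVA residual SD is 65 × √[(1+r)/2]. At r = 0.5 this is 56.3 s.

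| r | Interaction power | ANCOVA power | n per arm for 80% (interaction / ANCOVA) |
|---|---|---|---|
| 0.3 | 0.807 | 0.94 | 17 / 12 |
| 0.5 | 0.807 | 0.90 | 17 / 13 |
| 0.7 | 0.807 | 0.865 | 17 / 15 |
| 0.8 | 0.807 | 0.845 | 17 / 16 |
| 0.9 | 0.807 | 0.83 | 17 / 16 |

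**Reading 2: 65 s is the SD of the post-programme score.** The interaction SD is 65 × √[2(1−r)]; the ANCOVA residual SD is 65 × √(1−r²). At r = 0.3 these are 76.9 s and 62.0 s.

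| r | Interaction power | ANCOVA power | n per arm for 80% (interaction / ANCOVA) |
|---|---|---|---|
| 0.3 | 0.67 | 0.84 | 23 / 16 |
| 0.5 | 0.81 | 0.90 | 17 / 13 |
| 0.7 | 0.95 | 0.98 | 11 / 10 |
| 0.8 | 0.994 | 0.997 | 8 / 7 |
| 0.9 | 1.00 | 1.00 | 5 / 5 |

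**Simulation check** (Reading 2, 17 per arm, 20,000 trials per r). Interaction against ANCOVA: 0.669 and 0.830 at r = 0.3, 0.809 and 0.893 at 0.5, 0.954 and 0.973 at 0.7. The ANCOVA values fall up to about 0.01 below the formula, which ignores chance baseline imbalance. The type I error of ANCOVA was 0.048 to 0.054.

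**The case against.** The strongest reply is that the planned method is valid and already uses baseline. In a randomised trial with two time points, the interaction is an unbiased test of ET against sham, and the baseline value enters through the change score. That stands: the issue is efficiency and the form of the reported effect, not bias.

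The gain also depends on an unknown r and an unstated type of SD, and it is small when r is high. That stands too. With 21 per arm fully analysed and 65 s as the SD of change, the interaction already has power of about 0.885, above the 80% target.

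Within-group d is descriptive and not a test, and the section does plan a between-arm chi-square comparison and CIs around means. This is fair, but neither of these provides an effect size for the between-arm difference in ESWT time.

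A reader might go further and infer that the tape will be judged from the group main effect, which averages in the pre-randomisation value and so targets 65/2 = 32.5 s, or from a Bonferroni-corrected comparison of the arms after the programme, which ignores baseline. Power would be far lower on some of these routes. The article does not say that efficacy will be read from either. Not naming the ANOVA term is detail that a condensed article may leave to the full protocol or analysis plan, so these worst cases are not part of the finding.

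**Conclusion.** The point holds as an inexpensive improvement. The planned interaction test is sound but wastes information: its variance exceeds that of ANCOVA for every r below 1. The gain at 17 per arm is material at r of 0.3 to 0.5 under either SD reading (0.10 to 0.17 in power). At r of 0.7 to 0.9 it is 0.02 to 0.06 if 65 s is the SD of change. If 65 s is the post-score SD, it is about 0.02 at r = 0.7 and negligible from 0.8 upward. These sizes rest on the assumed r, equal SDs over time, normal errors and the planning difference of 65 s.

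Separately from any power figure, the only effect size named does not measure what the trial sets out to estimate. Calling the plan unadjusted, or its primary test invalid, would go beyond what the article supports.

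**What to change.** - **Primary analysis:** ANCOVA of post-programme ESWT time on arm with baseline ESWT time as covariate. Report the adjusted between-arm difference with its 95% CI, tested at two-sided .05.
- **Other outcomes measured before and after:** use the same model.
- **Effect size:** report a between-arm effect size with CI. Keep within-group Cohen d and within-arm changes as description only.
- **If assumptions fail:** transform the outcome or use a rank-based ANCOVA, named in advance.

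**Cost.** No extra patients, visits or measurements, as baseline ESWT is already recorded. The price is one residual degree of freedom (31 instead of 32 at 17 per arm), an approximately linear baseline-outcome relation, and a check that the software named in the Statistical Analysis section fits the model. The change should be fixed before outcome data are analysed.

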**Methods:**

This is a protocol for a randomized, controlled, 2-arm, parallel, blinded assessor clinical trial. Individuals will be followed for 8 weeks, twice a week, with PR sessions lasting approximately 1 hour. Health status (COPD Assessment Test), health-related quality of life (Chronic Respiratory Questionnaire), and psychological distress (Hospital Anxiety and Depression Scale) will be assessed before and after the intervention. Then, exercise capacity will be assessed via the incremental shuttle walking test and endurance shuttle walking test, and participants will use a triaxial accelerometer (ActiGraph) for 7 days to assess physical activity in daily life. Subsequently, individuals will be randomized into ET or sham groups; both groups will complete a PR program (2 times per week for 8 weeks). The ET group will receive applications of ET, whereas the sham group will receive a nonelastic tape. Data will be presented as means and SDs or medians and IQRs. Intergroup comparisons will be performed using a 2-way ANOVA, followed by the Bonferroni post hoc correction test, or the Kruskal-Wallis test, followed by the Dunn post hoc test. The threshold for statistical significance will be set at 5%.

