## Methods

### Study Design and Participants

This is a protocol for a randomized, controlled, 2-arm, parallel, assessor-blinded clinical trial. Individuals with COPD will be screened and recruited at the pulmonology outpatient clinic of a tertiary hospital. The study protocol was developed in accordance with the SPIRIT (Standard Protocol Items: Recommendations for Interventional Trials) checklist guidelines.

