### Experimental Design

Clinical and anthropometric data will be collected during the participant interview. Participants will complete questionnaires to assess health status (COPD Assessment Test [CAT]), HRQoL (Chronic Respiratory Questionnaire [CRQ]), and anxiety and depression symptoms (Hospital Anxiety and Depression Scale [HADS]). Then, a complete pulmonary function test (body plethysmography), the incremental shuttle walking test (ISWT), and the endurance shuttle walking test (ESWT) will be carried out. Finally, individuals will use a triaxial accelerometer (ActiGraph GT9X) for 7 days to assess their PADL. Lastly, individuals will be randomly assigned to 1 of 2 groups: the ET group or the sham group.

At baseline and postintervention, assessments will be performed by a researcher who is not involved in individual recruitment or intervention. After inclusion, individuals will begin an 8-week PR program twice a week (Figure 1). Individuals in the ET group will have the ET placed before the beginning of the PR program, and the ET will be replaced every 7 days throughout the 8-week period. The sham group will receive a nonelastic tape of the same color and size at the same position in the chest wall at the beginning of the PR program, and the tape will be replaced every 7 days, similar to the ET group. At the end of the PR program, participants will repeat the same assessments, except for the ISWT. The ESWT will be performed at the same level established by the ISWT during the initial evaluation (Figure 2).

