**Figure 2. F2:**
[figure not shown]
Schematic representation of the study design. Assessments were performed at baseline and after 8 weeks of intervention. 1RM: 1 repetition maximum test; CAT: COPD Assessment Test; CRQ: Chronic Respiratory Questionnaire; ET: elastic tape; ESWT: endurance shuttle walking test; HADS: Hospital Anxiety and Depression Scale; ISWT: incremental shuttle walking test; PAL: physical activity level; PR: pulmonary rehabilitation; PFT: pulmonary function test; V: visit.

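### The fallback for violated assumptions (Kruskal-Wallis with Dunn) does not match the two-arm, pre-post design: as written it drops the pairing and the group-by-time contrast, and the planned power would not carry over to it

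*Protocol article*

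**What the plan says.** The trial is a "randomized, controlled, 2-arm, parallel, assessor-blinded clinical trial". The Figure 2 legend states that "Assessments were performed at baseline and after 8 weeks of intervention". Under Experimental Design, "At the end of the PR program, participants will repeat the same assessments, except for the ISWT", so the ESWT is the walking test with both a baseline and a week-8 value. The Sample Calculation section treats it as the primary outcome and rests on "a mean difference of 65 (SD 65) seconds between groups in the ESWT".

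The Statistical Analysis section first sets the check on assumptions: "Data normality will be assessed using the Shapiro-Wilk test, and homoscedasticity will be assessed using the Levene test". It then gives the comparison and its replacement: "2-way ANOVA for repeated measures with Bonferroni post hoc correction or the Kruskal-Wallis test with Dunn test when assumptions are violated". The Abstract (Methods) has the same replacement: "or the Kruskal-Wallis test, followed by the Dunn post hoc test". Neither place says which values enter the Kruskal-Wallis test. Change scores appear in that section only for the Spearman correlations.

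**The concern.** The main analysis and its fallback do not test the same thing. With two arms and two time points, the repeated-measures ANOVA contains a group-by-time interaction, which asks whether the tape arm changed more than the sham arm. Kruskal-Wallis has no subject factor and no interaction term, so it is not the rank counterpart of that ANOVA.

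The fallback would apply to the primary outcome whenever the assumption checks fail. The trial's main question would then be answered by a test that either does not isolate the tape effect (the overall P value) or isolates it with far less power than planned (Dunn at week 8).

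**Working it through.** **1. The plan's own figure.** Difference 65 s and SD 65 s give a standardised difference of 65/65 = 1.0. A two-sample t-test with two-sided alpha 0.05 and power 0.80 (the plan labels .80 as beta; it is read here as power) needs 16.7, so 17 per arm. Power at 17 is 0.807. Adding 20% gives 17 × 1.20 = 20.4, so 21. The stated 17 and 21 are reproduced. They belong to a two-group comparison of means.

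**2. What the main analysis tests.** With two time points, the interaction F test equals the square of the two-sample t statistic on individual changes. If the SD of 65 s is the SD of change, its power at 17 per arm is the 0.807 above.

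**3. What the fallback could mean.**

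| Data entered | Pairing kept | Group-by-time tested | Role for Dunn |
|---|---|---|---|
| Four arm-by-time cells | No | No | Yes, six pairs |
| Week-8 values, two arms | No (baseline ignored) | No | None |
| Individual changes, two arms | Yes | Yes (equals Mann-Whitney) | None |

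Naming Dunn points to the first row. The third row is the valid counterpart of the ANOVA interaction.

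**4. Why Dunn is weak on four cells.** With n per cell and N = 4n, Dunn's statistic is the difference in mean ranks divided by √[N(N+1)/12 × 2/n]. For n = 17, N = 68: 68 × 69/12 = 391; 391 × 2/17 = 46; √46 = 6.78. Bonferroni for six pairs sets the two-sided level at 0.05/6 = 0.0083, so |z| must exceed 2.64. The mean ranks must differ by 2.64 × 6.78 = 17.9. Suppose the common gain is large enough that all week-8 values outrank all baseline values. The two week-8 cells then share the top 34 ranks, and even complete separation between them gives a difference of only 17. The comparison cannot reach significance in that case. For n = 21 the threshold is 2.64 × √(595 × 2/21) = 2.64 × 7.53 = 19.9, against a maximum of 21. The larger the shared gain, the less room is left for the tape effect.

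**5. Simulation.** Assumptions not given in the document: normal data; the SD of 65 s is the SD of change; pre-post correlation 0.7, so the SD of ESWT time is 65/√(2 × 0.3) = 83.9 s; a common rehabilitation gain of 65 to 100 s; correction for six pairs. For a true 65 s tape effect:

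| | 17 per arm | 21 per arm |
|---|---|---|
| Dunn, tape vs sham at week 8 | about 7% to 17% | about 10% to 25% |
| Mann-Whitney on change | about 78% to 79% | about 86% to 88% |

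With no tape effect and 17 per arm, the four-cell overall P is below .05 in about 79% to over 99% of trials, because it detects the shared gain. Dunn's week-8 comparison is falsely significant in about 1% or fewer.

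**6. Sensitivity (17 per arm, 3,000 trials per setting).** At correlations 0.5, 0.7 and 0.9, Dunn's power is 0.07, 0.07 and 0.05 with a 100 s common gain, and 0.50, 0.29 and 0.08 with none. Mann-Whitney on change stays at 0.78 to 0.79, with type I error 0.04 to 0.06. Kruskal-Wallis on week-8 values alone has about 0.78, 0.57 and 0.24.

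**The case against.** The four-cell analysis is inferred, not stated. The section calls these intergroup comparisons, and on two groups of change scores Kruskal-Wallis would be Mann-Whitney, with Dunn merely redundant. This stands as a qualification. The text does not say that changes are used, and naming a multiple-comparison test points the other way, so the rule is at best undefined between a valid and an unsuitable analysis.

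A reader might infer that the trial loses its primary comparison. The document does not support that. The repeated-measures ANOVA keeps the interaction, the fallback matters only if it is triggered, and even then a valid, unadjusted week-8 comparison of randomised arms survives.

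A reader might also take the 79% to over 99% as a false-positive rate for the tape. It is not one. The overall test detects the shared gain, as the time effect in the ANOVA also would, and the plan does not propose to read it as a tape effect.

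The power figures are illustrative. They use normal data, although the fallback is meant for data that fail the checks. On normal, equal-variance data, Shapiro-Wilk in each cell plus Levene triggers the switch in only about 20% of trials. The plan does not say whether the SD of 65 s refers to change or to ESWT time. If it is the SD of ESWT time, Dunn's power with 21 per arm is about 34% to 36% at a 65 s gain, 15% to 16% at 100 s, and 63% to 66% with no common gain. To claim almost no power in every setting would therefore go too far. The direction does hold: in these settings Dunn stays below Mann-Whitney on change.

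**Conclusion.** The point holds as a defect in a stated rule, conditional on the fallback being used. Kruskal-Wallis with Dunn is not a rank version of the planned repeated-measures ANOVA. In the only form that gives Dunn a role, it discards the pairing and has no group-by-time contrast. This follows from the design and does not depend on the simulation.

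The size does depend on assumptions. With correlation 0.7, SD of change 65 s and a common gain of 65 to 100 s, the surviving week-8 comparison falls well short of the planned 80% at either sample size, while a rank test on change roughly keeps it. The document gives no basis for saying how often the fallback would be triggered on real ESWT data, so no overall loss of power for the trial can be stated.

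**What to change.** In the Statistical Analysis section and the Abstract, state that the primary comparison is the group-by-time contrast on ESWT time (tape versus sham, change from baseline to week 8). Replace Kruskal-Wallis/Dunn with a fallback that keeps this contrast, for example Mann-Whitney on individual changes with a Hodges-Lehmann difference and 95% CI, or a rank-based or permutation ANCOVA. The Mann-Whitney power of 0.78 to 0.79 at 17 per arm shows that no material change in sample size is needed.

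An optional further improvement is to pre-specify baseline-adjusted ANCOVA as the single primary test and drop the normality and variance checks as a switch between tests. The defect itself does not require this.

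The cost is analysis wording only. With 10 participants recruited by November 2025 and results expected in November 2026, the wording can be settled before the data are analysed.

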### Analysis of the Population

The inclusion criteria will be as follows: diagnosis of moderate to very severe COPD [1], clinical stability (ie, no exacerbations for at least 30 days), male sex, nonobese status (BMI ≤29.9 kg/m^2^), absence of musculoskeletal limitations, and no participation in another research protocol or a PR program in the past 6 months. The exclusion criteria will be decompensated cognitive, neurological, and/or cardiological dysfunction and receiving home oxygen therapy. An intention-to-treat analysis will be performed using the patient’s most recent assessment in case of study dropout or absence of data and will be treated by imputing the last observation carried forward [14].

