Resistance training will consist of exercises for the upper limbs through lifting weights with dumbbells and for the LLs via weight machines. Large muscle groups will be trained, including the biceps, deltoids, quadriceps, and hamstrings. Training will begin with 3 sets of 8 repetitions of each exercise at a workload of 50% of the one-repetition maximum [18]. The number of repetitions will subsequently increase to 3 sets of 10 and, later, 12 repetitions. Load progression will be carried out when the individual tolerates performing more than 12 repetitions for each set without compensatory movements and/or symptoms of intolerance. The workload will be increased according to individual tolerance.

Resistance training for the upper limbs will include shoulder abduction and elbow flexion. Resistance training for the LLs will include knee extension and hip extension using “leg press” equipment.

No written material will be provided to either group. Transportation expenses will be subsidized for all individuals to reduce absenteeism and increase feasibility and adherence to the protocol. This financial resource will be funded for this research project. For analysis of the results, individuals must complete at least 80% (13 sessions) of the program, which will be monitored using the PR monitoring form, where data on HR, SpO_2_, the Borg scale, speed, and treadmill incline will be tabulated every 5 minutes, from the beginning to the end of the training session for all sessions.

The acceptability of ET use will be monitored throughout the session based on a visual inspection performed by the physiotherapist at the beginning of the session and during ET replacement every 7 days to immediately identify any skin changes that the individual may experience due to continued ET use.

To ensure or increase adherence to the 8-week PR program, the importance and potential benefits of PR, as established in the literature, will be explained to each participant individually, regardless of the group they are allocated to after randomization. Throughout the PR program, individuals will have a WhatsApp contact available to clarify and assist with any questions regarding their COPD-related health status. In cases of clinical worsening, the individual will be taken to the hospital emergency room for immediate medical care.

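### Carrying baseline forward puts no-change pairs into the exploratory Spearman correlations and can lift their false-positive rate above 5%

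*Protocol article*

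**What the plan says.** The Statistical Analysis section of the protocol article plans change-against-change correlations: "The Spearman correlation coefficient will be used to analyze the associations between changes in ESWT time and changes in CAT, HADS-A, HADS-D, and CRQ scores". It closes with a general rule and makes no exception for them: "Analyses will be conducted according to the intention-to-treat principle, using GraphPad Prism version 5.0, with significance set at *P*<.05".

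Analysis of the Population deals with dropout and absent data, which "will be treated by imputing the last observation carried forward". The caption of Figure 2 gives the visit schedule: "Assessments were performed at baseline and after 8 weeks of intervention". Sample Calculation expects imputed cases: "To account for potential losses and to allow for data imputation under the intention-to-treat principle, the sample size was increased by 20% in each group".

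The PR Program section sets a different condition for entering the analysis: "For analysis of the results, individuals must complete at least 80% (13 sessions) of the program".

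The text does not say whether the correlations are pooled over arms, run by arm or adjusted for arm. The Discussion labels the quality-of-life, anxiety and depression outcomes exploratory and advises caution because power may be low.

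**The concern.** With one post-baseline assessment, the last observation of anyone who misses week 8 is the baseline value. The imputed change is therefore zero on ESWT time and zero on every questionnaire. Such a pair holds no observed change and says nothing about whether gains in endurance go with gains in symptoms or quality of life.

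The pair is not neutral, however. The protocol expects rehabilitation to improve exercise capacity and quality of life in both groups. A block of pairs at zero on both axes then lies at the no-gain end of both rankings. The rank correlation it produces points towards benefit: positive for CRQ, and negative for CAT and HADS, where lower scores are better.

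A significant coefficient would be read as evidence that better endurance goes with better health status. At least four such tests are planned. All use the same ESWT changes and the same imputed pairs, so where several questionnaires improve on average, false positives would tend to occur together and look like corroboration.

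**Working it through.** **Plan's own sample size.** Sample Calculation gives a "mean difference of 65 (SD 65) seconds between groups in the ESWT", "considering an alpha of .05 and a beta of .80" (read here as power 0.80; two-sided alpha assumed).
- Normal approximation: n = 2 × (1.960 + 0.842)² × (65/65)² = 15.7, so 16 per arm. The t-based calculation gives 16.7, so 17, as stated.
- Inflation: 17 × 1.2 = 20.4, so 21 per arm and 42 in total, as stated.
- A 20% loss is 0.2 × 21 = 4.2, so about 4 per arm. That leaves 17 per arm, or 34 observed pairs.

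**Size of the artefact by formula.** Let q be the fraction carried forward. Let completers' changes, coded so that positive means improvement, be independent normals with SD 1 and means a (ESWT) and b (questionnaire). Ranks are expressed as fractions of the sample.
- On ESWT, dropouts lie on average (1 − q)[Φ(a) − ½] below the middle rank, and completers q[Φ(a) − ½] above it. The same holds for the questionnaire with b.
- Covariance of the ranks: q(1 − q)[Φ(a) − ½][Φ(b) − ½].
- Variance of the ranks, allowing for the tied block: (1 − q³)/12.
- Spurious rho = 12 q(1 − q)[Φ(a) − ½][Φ(b) − ½] / (1 − q³).

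With 4 dropouts per arm, q = 8/42 = 0.190 and 12q(1 − q)/(1 − q³) = 1.863:
- a = b = 0.5: 1.863 × 0.1915² = 0.068
- a = b = 1: 1.863 × 0.3413² = 0.217
- a or b = 0: exactly 0

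With 2 per arm, q = 4/42 = 0.095 and the factor is 1.035. At a = b = 1, rho = 1.035 × 0.3413² = 0.121.

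**Rejection rate by simulation.** At least 20,000 trials per setting, two-sided 5%, no true association and no tape effect. The mean gains are assumptions, because the document gives none in SD units.

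| Set analysed | Carried forward | Mean gains (SD), ESWT / questionnaire | Mean rho | Rejection |
|---|---|---|---|---|
| 42 pairs | none | 1 / 1 | 0.00 | 5.0% |
| 42 pairs | 4 per arm | 0.5 / 0.5 | 0.07 | 9.1% |
| 42 pairs | 4 per arm | 1 / 0.5 | 0.12 | 12.9% |
| 42 pairs | 4 per arm | 1 / 1 | 0.22 | 27.6% |
| 42 pairs | 4 per arm | 1 / 0 | 0.00 | 5.8% |
| 42 pairs | 2 per arm | 0.5 / 0.5 | 0.04 | 6.2% |
| 42 pairs | 2 per arm | 1 / 1 | 0.12 | 11.0% |
| One arm, 21 pairs | 4 | 1 / 0.5 | 0.12 | 8.5% |
| One arm, 21 pairs | 4 | 1 / 1 | 0.22 | 15.6% |
| Observed pairs, 34 | excluded | 1 / 1 | 0.00 | 5.1% |
| Observed pairs, one arm, 17 | excluded | 1 / 1 | 0.00 | 5.2% |

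The simulated mean rho agrees with the formula. Repeat runs with other seeds gave 9% to 10% at 0.5/0.5 and 28% to 29% at 1/1 with 4 dropouts per arm, and 10% to 11% at 1/1 with 2 per arm. When either measure has zero mean change, rejection with 4 per arm stays between 4.3% and 7.8% over the gains tried.

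**The case against.** **The excess is conditional.** A reader might infer that these tests will reject whenever no association exists. The documents do not support that. The excess needs enough dropouts and an average gain on both measures. The 20% is an allowance for losses, not a forecast, and the protocol gives no expected gain for any questionnaire; a gain on HADS in particular is an assumption. This objection stands and limits the claim to a range.

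**Pooling the arms.** A reader might also infer that one coefficient over both arms is an error, because a tape effect on both measures would produce a correlation even if gains were unrelated within each arm. With complete data, a 1 SD tape effect on ESWT and 0.5 to 1 SD on the questionnaire, a pooled test rejects in about 10% to 26% of trials. But the article does not say that the arms are pooled, and an article may leave that detail to a fuller plan. If the tape did move both measures, the changes really would be associated across the trial population, and detecting that is not a false positive. Larger figures obtained by combining pooling with carrying forward mix the two and should not be quoted as type I error. This objection stands in full.

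**The 80%-of-sessions rule.** If applied, it would remove most carried-forward pairs. However, it contradicts the intention-to-treat and carry-forward statements. It therefore leaves the correlation set undefined and does not cure the problem.

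**Low consequence.** The outcomes are exploratory and no between-arm conclusion rests on the correlations. That is correct and sets the severity. The Discussion's caution concerns insufficient power, though, and does not warn of spurious positives.

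**Conclusion.** The point holds in a limited form. Under the intention-to-treat and carry-forward rules as written, each participant with no week-8 data contributes a (0, 0) pair to every correlation. If completers improve on average on both measures, the test exceeds its 5% level: about 9% to 29% with 4 dropouts per arm and assumed gains of 0.5 to 1 SD on both, and about 10% to 11% with 2 per arm at 1 SD. There is little or no excess if one measure does not change on average. Running the correlations by arm does not remove the problem (about 9% to 16% in one arm of 21 with 4 dropouts, ESWT gain 1 SD and questionnaire gain 0.5 to 1 SD).

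The figures assume normal changes, dropout unrelated to outcome, and both week-8 measures missing together. The severity is minor: the analysis is exploratory and the primary comparison is unaffected.

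**What to change.** In Statistical Analysis, add to the correlation sentence that the coefficients will be computed only on participants whose ESWT time and relevant questionnaire score were both observed at baseline and at week 8, so that carried-forward values do not enter.

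Reconcile the 80%-of-sessions condition in PR Program with the intention-to-treat statements, so that the set used for the correlations is defined.

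Optionally, if a within-arm association is the aim, report the coefficient by arm or as a partial Spearman coefficient adjusted for arm. On observed pairs the partial version held 4.9% to 5.0% in every setting tried, including tape effects of 1 SD on both measures. The by-arm version needs only an ordinary Spearman coefficient. This is advice on the estimand, not a correction of an error.

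The cost is one sentence and fewer pairs: about 34 instead of 42 at 20% loss. None of the dropped pairs carries an observed change on both measures. With 10 participants recruited by November 2025, the change can be made well before analysis.
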